### Trial design {8}

SiFAr-Stress is a randomized controlled prospective study with a duration of 3 years and an additional part of the “Safer Cycling in Older Age [SiFAr]” intervention, described elsewhere (Siebentritt H, Keppner V, [name], [name], Rappl A, [name], et al. Safer cycling in older age (SiFAr): a protocol of a randomized controlled trial. BMC Geriatr. 2021. submitted). SiFAr is addressing the improvement of bicycle-related basic motor competence (e.g., balance, strength, ability to react, cycling skills, and techniques) to enhance cycling competence in older persons. SiFAr-Stress takes the opportunity to investigate and enhance the current knowledge of exercise intervention with regard to the effects on patho-biological level. The flow diagram for SiFAr-Stress is shown in Fig. 1.

**Fig. 1 Fig1:**
[figure not shown]
Flow diagram for SiFAr-Stress

## Methods: participants, interventions, and outcomes

### Study setting {9}

SiFAr-Stress is a controlled prospective study with parallel groups. The randomization of participants to an intervention (IG) or a control group (CG) will be stratified. The target populations of this study are community-dwelling older adults who are 65 years and older, who are living in the region of Nuremberg, Bavaria, Germany, and who participate in the SiFAr study. The participants of the main SiFAr study (Siebentritt H, Keppner V, [name], [name], Rappl A, [name], et al. Safer cycling in older age (SiFAr): a protocol of a randomized controlled trial. BMC Geriatr. 2021. submitted) will be identified by advertising the study in the local media (e.g., radio, newspaper, brochures) and by using a database of the study center. In addition, flyers will be displayed to specifically address potential participants. All participants of the main study will be offered to additionally participate in the sub-study. Participants additionally consent to give capillary blood, hair, and/or saliva samples. The study protocol was approved by the local ethics committee of the Friedrich-Alexander-Universität Erlangen-Nürnberg (number 22_20B). At the Institute of Biomedical Aging (IBA), participants take part in the assessment including questionnaires as well as functional and cognitive tests and capillary blood, hair samples, and saliva samples. All biological specimen analyses will be performed in the laboratory of the Chair of Health Psychology, Friedrich-Alexander-Universität Erlangen-Nürnberg. The study will be conducted in accordance with the Helsinki Declaration.

### Eligibility criteria {10}

The eligibility criteria of the SiFAr-Stress study are shown in Table 1.

**Table 1 Tab1:** Inclusion and exclusion criteria for SiFAr-Stress

Inclusion criteria	Exclusion criteria
- Age 65 years or older - Living in the area Nuremberg-Fürth-Erlangen, Bavaria, Germany - Ability to come to training locations on their own bicycle, having a suitable helmet - Participant is either: 1) a beginner with the e-bike 2) self-reported insecurity while cycling 3) a re-entrant in cycling - willingness to give biological samples	- Long-term, experienced cyclists without subjectively reported limitations or worries when cycling - Diseases that contradict safe participation in the intervention (e.g., myocardial infarction within the last 6 months, unstable angina pectoris, cerebrovascular event, serious cancer diagnosis, serious neurological diseases like Parkinson, dementia, and other serious new diagnoses) - Other factors that prevent regular and safe participation in the intervention (e.g., prolonged holidays during the training period, alcoholism) - Severe visual impairments that cannot be sufficiently compensated by a visual aid

### Who will take informed consent? {26a}

Participants will give informed consent after reading the participants’ information and after answering all participants’ questions in personal discussion with trained study staff at IBA.

### Additional consent provisions for collection and use of participant data and biological specimens {26b}

For biological specimens, participants sign an additional informed consent, where approval for each sample type, hair, capillary blood, and saliva, as well as for this data retention, is given separately. Conversely, participants are able to exclude one or more biological specimens.

### Interventions

#### Explanation for the choice of comparators {6b}

The control group receives the necessary information about secure cycling without the practical courses. This could be seen as standard care. Several exercise studies analyze the subjective perception and physiological parameters. SiFAr-Stress takes the opportunity to investigate and enhance the current knowledge of exercise interventions with regard to the effects on the patho-biological level.

#### Intervention description {11a}

SiFAr-Stress is an additional part of the SiFAr study following the time course of the main study. SiFAr consists of a practical and a theoretical part within 2 years. In the first year, the IG will participate in the multicomponent exercise program including cycling with a duration of 3 months, whereas the CG will take part in the theoretical course concerning bicycle-relevant lectures. Participants will be recruited from March to July. Both groups (IG + CG) will be tested for the performance in the cycling course and for functional and psychological parameters at T0 (before the intervention), T1 (after the 3-month intervention), and at 6 to 9-month follow-up (T2). To analyze stress- and health-related physiological parameters, biological specimen saliva, hair, and capillary blood will be collected. These patho-biological specimens will be collected during the intervention period to compare the change of different parameters during the intervention. The time points for biological specimen collection are identical as for functional and psychological parameters at T0, T1, and T2. The change of the concentration of stress hormone cortisol in the saliva specimen will be measured at T0 and T1. After completion of the intervention, all participants will be observed and tested as follow-up after 6 to 9 months.

Furthermore, short-term changes of cortisol concentration in the saliva specimens will be monitored for an acute-phase situation (prior, immediately after, and 20 min after the training session). The acute-phase situation will be determined twice during the training period, at the second and the second last training lesson. Therefore, the influence of the exercise training on the acute cortisol response in saliva will be determined.

In addition, hair specimens will be analyzed compared to longitudinal cortisol concentration. The inflammatory marker CRP will be analyzed in the capillary blood. The change in CRP concentration in the blood allows conclusions on inflammatory processes in the body.

### Assessments

The baseline assessment includes general information on sociodemographic variables age, sex, education, living situation, and family status. Anthropomorphic measurements (weight, height), quality of life, health status, tests for physical performance, and functional tests as well as psychological and cognitive status are performed at baseline as well as at follow-up. In addition, objective and self-reported information on cycling habits will be obtained.

#### Assessments of biomedical, anthropometric, and functional health variables

##### Health status

In order to record the health status, the number of diseases and medication will be determined by questionnaire.

##### Recent fall experiences

A fall will be defined as an unexpected event in which the participant comes to rest on the ground, floor, or lower level. We will assess whether participants have experienced a fall event in the 12 months prior to enrollment by a standardized questionnaire used in all our previous studies. If a fall has been taken place, we will ask for the severity of the injuries.

##### Physical performance

Physical performance will be assessed via the Short Physical Performance Battery (SPPB). The SPPB is a brief performance battery based on a set of functional tasks related to the lower extremities. It includes static balance tests, timed short distance walk, and repeated chair stands and hence can be used to assess how well older persons perform simple movements that represent the building blocks of daily activities that require good lower extremity function. Each of the three test domains is scored from 0 (inability) to 4, and a sum score of the three domains is obtained for each participant (0–12). The battery has been used in many studies, and it has a high predictive validity and prognostic value [30]. In addition, one leg stand is performed.

##### Health-related quality of life (HRQoL)

HRQoL will be measured with the EURQOL (EQ-5D) which has been used in the IBA in many studies. The EQ-5D has very good measurement properties and is widely used [31]. The sum score and visual analog scale (VAS, 0–100) will be determined. HRQoL is lately regarded as a critical outcome in contemporary medical research.

### Assessment of cycling related parameters

#### Frequency of bicycle use

A bicycle computer will measure kilometers driven within the 3 months of the intervention period.

#### Questionnaires related to cycling behavior

Cycling behavior will be assessed by questionnaires concerning bicycle type, cycling behavior, mobility biography, and history of accidents.

### Baseline assessment of general psychological status

#### Depressive symptoms

Age-related declines in mobility and functional health tend to be associated with symptoms of depression. We will therefore use the Geriatric Depression Scale (GDS-15), which is appropriate for the age group in our project and was shown to have good sensitivity and specificity [32, 33].

#### Perceived stress

In addition to depression, we will also assess general perceived stress. The perceived stress scale (PSS) is the gold standard for the assessment of sub-chronic life stress in adults [34, 35], and has been validated for older adults as well [36]. We will use the 10-item version as a global assessment of perceived stress, with which the sum scores could be assessed on a scale between 0 and 40. Higher scores indicate higher perceived stress with cutoff points 0–17 reflecting low and 17–40 high perceived stress [34] for older adults aged 60–69 years and 0–15 reflecting low and 15–40 high perceived stress for older adults aged 70 years or older.

### Assessment of fear of falling

#### Fear of falling

As a measure of fear of falling, we will use the current gold standard, the short FES-I scale, which is a 7-item questionnaire related to concerns about falling during basic and more demanding daily activities among independent, community-dwelling older persons. We will use the validated German version of the FES-I [37]. We will analyze the mean change in the sum score (7–28 points) between baseline and 3 months follow-up. Delbaere et al. established cutoff points, 7–8 low concern, 9–13 moderate concern, and 14–28 high concern [38].

### Assessment of cognitive functions

#### Mild cognitive impairment (MCI) screening

The Montreal Cognitive Assessment (MoCA) will be used as a screening tool for MCI. The MoCA yields sum scores between 0 and 30 and is a high-sensitive screening tool [39]. Sum score 26 and higher is considered to be normal, and ≤ 25 indicates cognitive impairment.

#### Executive functions

The Trail Making Test (version A and B) of the CERAD will be used to monitor executive function and mental flexibility since this test was shown to be sensitive to a variety of neurological impairments and processes [40]. In this test, the time and number of faults are monitored.

### Assessment of stress and stress-related pathophysiological processes

#### Stress system activity

Chronic stress has a profound effect on the HPA axis. We will assess the basal activity of the HPA axis using non-invasive, at-home saliva samples measuring salivary cortisol, for example, documented in [41] as well as the collection of hair cortisol samples.

During the first appointment, participants will receive a home sampling package containing detailed instructions, two salivettes (Sarstedt, Nümbrecht), and a pre-stamped envelope for returning samples. In brief, at each time point during the study (T0, T1, and T2), participants were instructed to collect saliva specimens by means of salivettes at two consecutive days prior to bedtime. One hour before saliva sample collection, participants were asked not to eat, drink (except water), smoke, or brush their teeth. Salivettes are kept and moved in the mouth for at least 1 min without chewing on it. During saliva collection, participants will be asked to rate their subjective stress perception. For this, established protocols and instructions that have been used in previous research on older adults will be used [42]. Participants collect the bedtime samples at home and store them in the fridge until all the saliva samples are collected and sent them by postal mail to the study center. Immediately after arrival, saliva samples will be stored at − 30 °C for later analyses. Salivettes will be thawed and centrifuged at 2000*g* at 4 °C. Cortisol concentration in nmol/L will be analyzed in the salivary specimen using commercially available high-sensitive ELISA (Enzyme-linked immunosorbant assay).

Hair sample collection is carried out as previously described by Greff et al. [43]. In brief, hair specimens are cut as close to the scalp as possible after sectioning off the hair at the posterior vertex. A sample of at least 3 cm of length is collected in order to cover a 3-month time period. After extraction, HCC will be measured by ELISA [43, 44]. At the time of hair sample collection, a questionnaire is answered to obtain information on hair-related factors influencing hair steroid hormone concentrations. The questionnaire includes hair washing frequency, application of hair dye, or any other chemical treatment.

On the second and seventh training lessons (tr2 and tr7), participants will provide three saliva samples at three time points (before the training, immediately after the training, and 20 min after the training). Furthermore, perceived stress and anxiety will be rated on 10-point Likert scales, which have been used in previous research at the Chair of Health Psychology [45–48]. From the saliva samples, sAA and cortisol will be assessed as measures for SNS and HPA axis activity. The concentration of sAA will be measured with an enzyme kinetic assay, as previously described [41, 49], and salivary cortisol using a high-sensitive ELISA provided by IBL International according to the manufacturers’ instructions.

#### Systemic inflammation

Systemic low-grade inflammation will be measured by the CRP concentration of capillary blood specimens. Dried blood spot samples will be collected by a minimal invasive finger stick. Therefore, drops of capillary whole blood samples are collected on filter paper and dried [27]. Concentrations of CRP in the blood specimen are carried out by high-sensitive ELISA as described by McDade et al. [26].

A trained study nurse collects all biological specimens as part of the assessment.

### Repeated assessments at T1 and T2

All measures taken at baseline will be repeated at T1 and T2 except for sociodemographic variables. Therefore, changes of variables over a period of 3 months and after a follow-up period of 6 to 9 months will be analyzed.

### Criteria for discontinuing or modifying allocated interventions {11b}

Criteria for discontinuing the intervention for a given participant are adverse event–like accident with severe injuries (e.g., fractures), serious illness, and quarantine (coronavirus) preventing to participate in the intervention.

### Strategies to improve adherence to interventions {11c}

At the first appointments at IBA, the personal meeting includes explanation and practical instruction of saliva sampling procedure as well as a detailed set of written instructions, and a brief questionnaire asking participants for sampling times for reference at home is provided. In addition, participants receive a prepaid envelope to return saliva samples. Close communication via phone calls will be applied, if saliva samples were not returned after a certain period. For the assessments and testing, participants receive personal reminder calls, if desired.

### Relevant concomitant care permitted or prohibited during the trial {11d}

Many factors are known to potentially influence saliva cortisol measurement, like tooth brushing, eating, drinking caffeinated drinks, and ordinary physical activity. We therefore ask participants to avoid eating, drinking (except water), smoking, chewing gum, and brushing teeth for at least 1 h before saliva sampling.

### Provisions for post-trial care {30}

Not applicable

### Outcomes {12}

The primary outcome is the change in cortisol and between the beginning of the intervention (T0) and after the intervention (T1). As secondary outcomes, the mean changes in fear of falling (FES-I) and psychological parameters (sAA, CRP, stress (PSS)) over a period of 3 months (after the intervention) and after a follow-up period of 6 to 9 months will be analyzed. Furthermore, the acute effects on cortisol levels during a session at the beginning and at the end of the training intervention (Tr1 and Tr7) will be assessed.

Cycling accidents during the intervention period present a potential risk for the participants and therefore might be a potential harm outcome.

### Participant timeline {13}

The participant timeline is shown in Table 2.

**Table 2 Tab2:** Example template of recommended content for the schedule of enrolment, interventions, and assessments*

	Study period				
	Enrolment baseline	Intervention period			Post-allocation
Timepoint**	***T***_**0**_	***t***_***r*****2**_	***t***_***r*****7**_	***T***_**1**_	***T***_**2**_
**Enrollment**					
**Eligibility screen**	X				
**Informed consent**	X				
**Allocation**	X				
**Study arms**					
***Intervention group***	X	X	X	X	X
***Active control group***	X			X	X
**Assessments**					
***Sociodemographic characteristics***	X				
***Weight/height/BMI***	X			X	X
***Health parameters (medication, diseases)***	X			X	X
***Cognitive function (MoCA, TMT A&B)***	X			X	X
***Performance in the cycle course***	X			X	X
***Physical performance (SPPB)***	X			X	X
***Quality of life (EuroQoL-5D + VAS)***	X			X	X
***Falls/fear of falling (FES-I short form)***	X			X	X
***Bicycle-related Parameters (cycled distance, self-reported cycling behavior)***	X			X	X
***Biological specimen***					
***Saliva samples***	X	3*x*^1^	3*x*^1^	X	X
***CRP (capillary blood sample)***	X			X	X
***Hair sample***	X			X	X

*MoCA* Montreal-Cognitive Assessment, *TMT* Trail Making Test, *SPPB* Short Physical Performance Battery, *VAS* visual analog scale, *FES-I* Falls Efficacy Scale-International Version, *CRP* C-reactive protein

^1^Saliva samples only for intervention group

### Sample size {14}

For statistical analyses of the primary and secondary outcomes, 2-factorial repeated measures ANOVAs are planned (see {20a}). A power analysis for this statistical procedure has been conducted for sample size estimation (GPower 3.1.9.2). Due to the heterogeneity of older persons, the effect size (ES) in this study is estimated to be small to moderate (*f* = .3). With an *α* = .05 and power 1 − *β* = .80, the estimated sample size needed for this effect size is approximately *N* = 111 for a between-group comparison between IG and CG with a 1:1 allocation and three measurement time points. Based on an estimated drop-out rate of 20%, a sample size of *N* = 140 will be adequate for the main objective of this study and should allow for the expected drop-out rate.

### Recruitment {15}

Participants will be recruited exclusively from the SiFAr study’s participants. At IBA, established strategies for recruitment are advertisement in local media (e.g., radio, newspaper, brochures) and using an in-house database of the IBA. In addition, flyers are displayed to bicycle organizations and bicycle dealers to specifically address potential participants. SiFAr will have to recruit almost double of participants in the same time, which allows to meet the number of 140 for SiFAr-Stress according to a participation rate of the last year.

## Assignment of interventions: allocation

### Sequence generation {16a}

A statistician, who was otherwise not involved in the planning of the study design, generated computer-based randomization lists. The criteria for randomization of participants to IG or CG are gender and bicycle type (e-bikes/unmotorized bicycle), whereas couples are block-wise randomized to ensure the participation together in one group.

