## Data collection and management

### Plans for assessment and collection of outcomes {18a}

After completion of data collection for each time point, data entry will be performed contemporary to ensure identification of missing data and any discrepancies. This enables to record missing data or wrong inputs from participants. All data will be cleaned, inspected for outliers, and tested for normality of distribution prior to hypothesis testing. Composite scores, e.g., for questionnaires, will be computed where appropriate. Quality control for laboratory data is performed first by using standard procedures and second including intra- and inter-assay variability. Laboratory values not complying with quality control requirements will be repeated. The means and standard deviations for all variables will be computed, and preliminary analyses testing for age and gender effects will be performed.

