## Statistical methods

### Statistical methods for primary and secondary outcomes {20a}

Data analysis will be performed using descriptive statistical analysis and inferential statistics. The sample data will be presented by frequencies or percentages, means ± standard deviation or median and interquartile range, and graphics. The IBM® SPSS® Statistics for Windows, version 26 software (IBM Corp., Armonk, NY, USA) will be used for all statistical analyses.

For the evaluation of primary outcomes, 3 × 2 analyses of variance for repeated measurements (ANOVA) will be used: For evaluating the long-term changes in CRP and cortisol (hair and saliva), 2-factorial ANOVAs with the factors “time point” (T0, T1, T2) and “group” (IG or CG) will be conducted. For the evaluation of the acute effects of the training intervention, further ANOVAs with the factors “time point” (before, after, and 20 min after the training) and “training number” (second or seventh training) will be calculated. For the evaluation of further secondary outcomes, comparable analyses will be conducted.

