### Methods for additional analyses (e.g., subgroup analyses) {20b}

Not applicable

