A large number of factors may influence PSS as well as cortisol concentration: age, sex, smoking, BMI, ever diagnosis of depression, ever diagnosed cardiovascular disease, and time of day.

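### Randomisation uses gender, bicycle type and joint allocation of couples, but the IG–CG model contains only time point and group, so the analysis does not reflect the design

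*Protocol article*

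**What the plan says.** All places are in the protocol article.

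- **Design.** Study setting {9}: "The randomization of participants to an intervention (IG) or a control group (CG) will be stratified". Sequence generation {16a} names the factors: "The criteria for randomization of participants to IG or CG are gender and bicycle type (e-bikes/unmotorized bicycle". It adds that "couples are block-wise randomized to ensure the participation together in one group". Sections {16b} and {16c} confirm that stratification information is passed to the person who allocates.
- **Analysis.** Statistical methods {20a}: for hair and saliva cortisol and CRP, "2-factorial ANOVAs with the factors “time point” (T0, T1, T2) and “group” (IG or CG) will be conducted". Sample size {14} also describes a two-factor analysis, and {20b} plans no additional analyses.
- **Gender elsewhere.** In {18a}, "preliminary analyses testing for age and gender effects will be performed", with no statement of what follows from the result. Potential risks and limitations: "A large number of factors may influence PSS as well as cortisol concentration: age, sex, smoking, BMI". Bicycle type is not in that list and has no stated role in the analysis.
- **Primary question.** Objectives {7} and Outcomes {12} define it as the change in cortisol from T0 to T1, compared between the arms.

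**The concern.** An analysis should carry the features that constrained the allocation. Two of them are missing here, and they act on the standard error in different ways.

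1. Balancing the arms on a prognostic factor and then leaving it out keeps that factor's variance in the error term, although the allocation has removed it from the treatment contrast. The reported standard error is then too large and the test is conservative.
2. Partners allocated together are not independent units. A model that treats them as independent reports a standard error that is too small if their outcomes are positively correlated.

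At stake are the precision and the calibration of every IG–CG comparison in {20a}. That section writes out the list of factors, so this is a stated model and not a detail left to a later analysis plan.

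**Working it through.** **1. The plan's own figure.** Inputs from {14}: f = 0.3, α = .05, power .80, 20% drop-out. A fixed-effects ANOVA with 2 numerator df and noncentrality f²N = 0.09 × 111 = 9.99 has power .803, so N = 111 reproduces. 111/0.8 = 138.75, close to the stated 140. No stratum enters this calculation.

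**2. Group main effect.** Let R² be the share of between-subject variance explained by the strata. The documents give no value, so 5%, 10% and 20% are assumptions. With the strata balanced between arms:

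- reported SE / true SE = 1/√(1 − R²)
- actual type I error = 2[1 − Φ(1.96/√(1 − R²))]

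| Assumed R² | SE ratio | Type I error | Power at d = 0.5, unadjusted / adjusted | Power at d = 0.6 (f = 0.3), unadjusted / adjusted |
|---|---|---|---|---|
| 0 | 1.00 | .050 | .750 / .742 | .885 / .879 |
| 5% | 1.03 | .044 | .755 / .764 | .891 / .895 |
| 10% | 1.05 | .039 | .761 / .786 | .897 / .910 |
| 20% | 1.12 | .028 | .774 / .831 | .910 / .938 |

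At these effect sizes the power forgone is between nil and about 6 points (.831 − .774 = .057).

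**3. Group × time, the term that carries the primary hypothesis.** Stratum effects that are constant over time cancel within a participant. This was checked by simulating the 3 × 2 ANOVA: n = 112 (0.8 × 140), four strata balanced between arms, within-person correlation 0.5, an effect of 0.42 SD at T1 and T2, 4000 runs. Any stratum × time effect was put in a straight trend from T0 to T2. Adjustment used stratum and stratum × time terms. All these settings are assumptions.

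| Stratum effects | Type I error, unadjusted / adjusted | Power, unadjusted / adjusted |
|---|---|---|
| Constant over time, R² = 20% | .054 / .050 | .62 / .61 |
| As above, plus stratum × time = 5% of within-subject variance | .035 / .054 | .61 / .65 |
| As above, plus stratum × time = 10% of within-subject variance | .025 / .054 | .58 / .66 |

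The Monte Carlo standard error is √(.05 × .95/4000) ≈ .003 for type I error and √(.6 × .4/4000) ≈ .008 for power. The first row therefore shows no real difference. The other two show a loss.

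**4. Couples.** For pairs, the design effect is about 1 + p × ICC, where p is the share of participants who belong to a couple. Neither quantity is in the documents. With p from 10% to 50% and ICC from 0.1 to 0.5, it runs from 1 + 0.1 × 0.1 = 1.01 to 1 + 0.5 × 0.5 = 1.25.

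**5. Both together.** For the group main effect, taking the ICC as the correlation left after the strata, reported SE / true SE ≈ 1/√[(1 − R²)(1 + p × ICC)].

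- R² = 20%, design effect 1.01: 1/√(0.80 × 1.01) = 1/√0.808 = 1.11, too large.
- R² = 20%, design effect 1.25: 1/√(0.80 × 1.25) = 1.00.
- R² = 5%, design effect 1.25: 1/√(0.95 × 1.25) = 1/√1.1875 = 0.92, too small.

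The sign of the net error depends on inputs that the documents do not give.

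**The case against.** The strongest defence is that the primary outcome is a change, and in a repeated-measures ANOVA the group × time term already removes any constant effect of gender or bicycle type. This stands. It means the figures in step 2 do not describe the primary test. A reader might infer that 6, 11 or 22 of the 111 participants are wasted (111 less the 105, 100 or 89 that the formula behind 111 would need after adjustment). The documents do not support that for the primary comparison: those counts belong to a between-subject effect under an assumed R².

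Four further readings go too far.

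- **That the tests are conservative.** This overlooks the couples, whose joint allocation pushes the other way. It also needs balance in the analysed set, which is not assured: participants volunteer from the main study, consent separately to each specimen, and are excluded for non-adherence {20c} or, for cortisol, glucocorticoid use.
- **That {18a} selects covariates from preliminary tests.** It says only that the tests will be done. It leaves their consequence open.
- **That stratification by gender fails for mixed couples.** Such a couple adds one man and one woman to the same arm and does not by itself unbalance gender.
- **That both factors are known to be prognostic.** Sex is named as a possible influence on cortisol. Bicycle type is not.

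The defence does not remove the point. The trial's own rationale makes a time-varying effect of bicycle type conceivable: the background names a change to a motorised bicycle as a stressor, e-bike beginners are eligible, and the objectives expect training-related anxiety to fade. That is a reason to allow for such an effect, not evidence that it exists. The couples are not dealt with in the stated model at all.

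**Conclusion.** The mismatch between design and model holds: two stratification factors and the pairing of couples shape the allocation, and none appears in {20a}. Its size is conditional.

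- For the group main effect, the standard error is overstated by about 3% to 12% if the strata explain 5% to 20% of variance and are balanced in the analysed set.
- For the primary group × time comparison, nothing is lost if stratum effects are constant. About 4 to 8 power points are lost if stratum × time explains 5% to 10% of within-subject variance.
- Ignoring couples works in the other direction, with a design effect of about 1.01 to 1.25 under assumed shares and correlations.

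The net direction of the error is therefore undetermined. Omitting the strata does not by itself inflate false positives; ignoring positively correlated partners could. The case for changing the plan is that the correction is inexpensive and can be fixed before results are seen, not that a large error has been shown.

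**What to change.** In {20a}, for each outcome compared between IG and CG:

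- Model the post-baseline values (T1, and T2 where analysed) with group, time and group × time.
- Adjust for the T0 value, gender and bicycle type, with their time interactions if more than one post-baseline time point is modelled. T0 then leaves the time factor, because it cannot be both a covariate and a level of that factor.
- Account for couples as clusters, by a random effect or cluster-robust standard errors. A yes/no term for being in a couple would not handle the correlation between partners.

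In {18a}, state that the preliminary age and gender tests are descriptive and do not determine the model.

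The cost is a mixed model in place of the simple ANOVA and a few degrees of freedom: one each for T0, gender and bicycle type, and as many again if each has a time interaction over two post-baseline visits. The stratification factors are known at randomisation and T0 is measured before it, so no new data are needed beyond a couple identifier, which joint allocation already requires. The acute-session analyses involve the intervention group only and have no IG–CG comparison to adjust.
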